## Abstract

**Background:**

The co-occurrence of domestic violence with alcohol and other drugs significantly increases the severity of abuse and violence experienced by family members. Longitudinal studies indicate that substance use is one of few predictors of men’s continued use of, or desistance from, violence. Recent developments in men’s behaviour change programs have focused on men’s attitudes and behaviour towards their children, and the exploration of interventions that address the needs of all family members. However, the research evidence is limited on the most effective elements of men’s behaviour change programs in promoting the safety and wellbeing of child and women victim survivors.

This study aims to build on the existing evidence by trialling the KODY program which addresses harmful substance use by men who also perpetrate domestic violence; the safety and wellbeing of women and children; the needs of children in their own right, as well as in relationship with their mothers; and the development of an ‘all-of-family’ service response. The evaluation of these innovations, and the ramifications for policy development to support less fragmented service system responses, provide the rationale for the study.

**Methods/Design:**

A quasi-experimental design will be used to assess the primary outcomes of improving the safety and wellbeing of mothers and children whose (ex)partners and fathers respectively participate in KODY (the trial program), when compared with ‘*Caring Dads* standard’ (the comparison group). Psychometric tests will be administered to fathers and mothers at baseline, post-program and at 3-month follow up. Data collection will occur over three years.

**Discussion:**

By building the evidence base about responses to co-occurring domestic violence and substance use, this study aims to develop knowledge about improving safety outcomes for women and children, and to better understand appropriate support for children in families living at the intersection of domestic violence and substance use. It is anticipated that study findings will point to the ramifications for policy development to support less fragmented service system responses.

**Trial registration:**

An application for registration with the Australian and New Zealand Clinical Trials Registry (https://www.anzctr.org.au/) was lodged on 20 December 2021 (Request number: 383206)—prospectively registered.

## Background

The co-occurrence of domestic violence (DV) with alcohol and other drugs (AOD) significantly increases the severity of abuse and violence experienced by family members [1]. Programs for men who use violence generally focus on addressing the violence and abuse directed at women (their partners or ex-partners), while children, who make up 50% of those affected, are rarely in focus [2].

A new wave of programs for men who use violence which focus on their fathering, attitudes and behaviour towards their children, has seen *Caring Dads* programs developed by Scott, Kelly, Crooks and Francis (2018) in Canada, and adapted and evaluated in Australia and internationally [3–7]. The recent evaluation of the *Caring Dads* program in Australia identified a range of issues which the proposed innovative program and evaluation seeks to address to improve health and wellbeing outcomes and the effectiveness of the program. These include a) the problems associated with the co-occurrence of DV with AOD issues; b) the requirement to develop safe ‘all-of-family’ responses, particularly for families who are not separating; c) the lack of attention to the support needs of children whose fathers are attending *Caring Dads*; and d) the requirement for evaluation measures for programs to address fathering, DV and AOD.

The quasi-experimental trial discussed in this paper was designed to pilot and evaluate an all-of-family response to the complex issues for children, women and men living with AOD and DV. The KODY program (Kids First (*Caring **D**ads*) and Odyssey House Victoria) integrates and enhances the work of two non-government organisations in Melbourne, Australia. Kids First Australia auspices a *Caring Dads* program. Odyssey House Victoria provides a range of alcohol and other drug treatment programs including services for parents affected by problematic substance use and their children, such as *Kids in Focus*, a family centred program that emphasises the safety and wellbeing of children in addition to providing parenting and family support.

Victorian domestic homicide reviews indicate that between 50–60% of murders occur in the context of the use of alcohol or other drugs [8] suggesting an association between the severity of DV and the use of AOD. In longitudinal studies, AOD use has emerged as one of few consistent predictors of men’s continued use of, or desistance from violence [9, 10]. Substance use is also associated with negative, hostile and aggressive parenting [11, 12]. The Australian *Caring Dads* evaluation for fathers who use violence found that a third of participants were accessing AOD services [6]. Some groups are over-represented in their need for these services. A significant proportion of the *Kids in Focus* clients at Odyssey House Victoria come from Aboriginal or culturally and linguistically diverse (CALD) backgrounds. In addition, a considerable number of men display co-occurring mental health issues [13]. Unemployed men who hold highly traditional notions of masculinity are also over-represented among users of harmful alcohol use and DV [10, 14, 15]. This body of research suggests the need to explore models of intervention that address both men’s substance use and their use of violence and coercive control [12].

There is widespread recognition that DV is predominantly a gendered issue of men’s violence towards women [2]. However, less attention has been given to children as victims of the destructive parenting behaviours of fathers who use domestic violence and coercive control [16]. The evidence is compelling and well established that children’s exposure has negative consequences for them [17]. These include adverse health impacts [18], the undermining of children’s emotional and psychological wellbeing [19], and problems connected with damaging behaviours. Similarly, the destructive impact for children living with parental harmful substance use is a significant driver of children into child protection and out of home care [20], particularly when there is co-occurrence with DV and carer mental ill-health [21, 22].

Despite the established importance of DV and AOD to child outcomes, comparatively little notice has been taken of attitudes and behaviours towards children in interventions for either of these problems. AOD programs, although well researched for their efficacy regarding reduced use of substances, have very seldom considered or included improved fathering and better child outcomes as a program or evaluation outcome. Recent overviews of research on men’s behaviour change (MBC) programs stress the need for robust evaluations of more targeted programs that respond to the diverse needs and characteristics of the men referred [23, 24]. Currently, it is unclear which elements of these programs work for which men, under what circumstances, and how they contribute to increased safety for women and children. There is evidence that some men are motivated by their desire to be a good father and that this can be a source of behaviour change [25]. Evaluations of the small number of programs for fathers who use violence show positive findings [3–7, 26].

A more recent, although still early, development in the area of MBC programming [27, 28] and other interventions in the DV area [29] has been the exploration of interventions for all family members. ‘All-of-family’ programs address the needs of each family member in their own right [26], going beyond the often-marginalised partner support component attached to MBC or *Caring Dads* programs and focusing on children as well as women victim survivors. The ‘all-of-family’ model is a DV-informed framework developed by the Safe and Together Institute to address the needs and responses to each family member living at the intersection of DV and AOD [30]. This approach is particularly appropriate when families are not in a position to separate [28, 31].

Through assessing the effectiveness of the innovative KODY program, this study aims to address many of these issues: harmful substance use by men who also perpetrate DV; the needs of children in their own right, as well as in relationship to their mothers through the Odyssey House Victoria *Kids in Focus* program; and the development of an ‘all-of-family’ service response. The evaluation of these innovations and the ramifications for policy development to support less fragmented service system responses provide the rationale for the proposed trial.

## Methods / Design

The primary aim of the study is to test the effectiveness of the KODY program in supporting safety for mothers and children with experiences of DV perpetrated by men with problematic substance use. It is hypothesised that the program will:

1) improve the safety and wellbeing of women whose (ex)partners participate in KODY *Caring Dads*;

2) improve the safety and wellbeing of children, whose fathers participate in KODY *Caring Dads*.

Secondary outcomes include fathers’ use of DV and of AOD (see Table 1).

**Table 1 Tab1:** Primary and Secondary Outcomes and measures

Outcomes measured	Outcomes Measures completed by Fathers	Outcomes Measures completed by Mothers
**Primary Outcomes**		
** Safety and well-being of women**		Composite Abuse Scale
** Safety and well-being of children**	Emotional Dysregulation Scale	Emotional Dysregulation Scale
	Interpersonal Mindfulness in Parenting Scale	Brief Infant–Toddler Social and Emotional Assessment
		* Strengths and Difficulties Questionnaire – ages 3 +
**Secondary Outcomes**		
** Fathers’ use of DV**	Mirabal measures (adapted)	Mirabal measures (adapted)
	Anger Management Scale	Composite Abuse Scale
	Brief Irritability Test	
** Fathers’ substance use**	Alcohol Use Disorders Identification Test (AUDIT)	
	Drug Use Disorders Identification Test (DUDIT)	

^*^ Adolescents involved with KODY will also be invited to fill in the appropriate version of the Strengths and Difficulties Questionnaire

The effectiveness of the KODY program will be tested with a quasi-experimental design comparing outcomes between KODY (the trial program) and ‘*Caring Dads* standard’ [32] (the comparison group). Due to the small-scale and innovative nature of the trial program, it was deemed impracticable and unethical to randomly assign participants to trial and comparison groups. Psychometric tests will be administered to men and women participants at three timepoints—baseline (T1), post-*Caring Dads* program (T2) and three months after the end of the *Caring Dads* program (T3). Supplementary analyses of participation data obtained through file reviews will be conducted to examine the extent to which intervention effects vary according to ‘dose’ level of expanded service. In the context of this trial, ‘dose’ levels refer to the number of group work sessions attended by fathers, the degree of engagement by mothers with the Child and Family Wellbeing Practitioner and the *Kids in Focus* activities in which children, mothers and fathers participate.

The program and outcomes measures will first be tested for feasibility. To add context to the findings of the quasi-experimental study, a process evaluation will also be conducted, drawing on interviews with children, women and men, as well as program administrative data. Data collection will occur over three years.

### The intervention

The trial intervention (KODY) is a new model of service that integrates the work of both Kids First and Odyssey House Victoria to address the complex issues for children, women and men living with AOD and DV. The ‘*Caring Dads* standard’ program (the comparison group) consists of the following components.

**Group work**—17 sessions, manualised content, focus on engaging men to examine their fathering, increasing child centred fathering, including respect and support of children’s mothers, and changing patterns of harmful fathering.

**Case Coordination**—case coordination between group intervention and mother contact practitioners.

**Services for mothers and children**—mothers of children with whom fathers have contact are provided support and safety planning through a Child and Family Wellbeing Practitioner.

KODY (the trial program) comprises the ‘*Caring Dads* standard’ program plus the following changes and additions.

**Group work**—‘*Caring Dads* standard’ program with added curriculum materials and specialist AOD facilitation of group sessions.

**Case Coordination**—Collaborative case coordination for fathers by KODY DV and AOD practitioners. Additionally, *Kids in Focus* offers all-of-family case management, which will be integrated with *Caring Dads* case coordination.

**Services for mothers and children**—In addition to support from the Child and Family Wellbeing Practitioner, linked intervention with all family members (children, mothers and fathers) through *Kids in Focus*, including parenting education and support and recreational and therapeutic groups for children and their families.

The intervention group will be implemented by a co-facilitation team with expertise in working with fathers to address DV and AOD. The comparison group will be implemented by professionals experienced in DV and the delivery of *Caring Dads*. Adherence to intervention protocols will be monitored through regular meetings with program staff, recording of participation across time and program components, and observation of selected KODY *Caring Dads* group sessions.

### Eligibility criteria

The target group for study is fathers who use DV and AOD. Fathers and their (ex)partners eligible to participate in either the trial or the comparison programs will be eligible for the study. In both groups, eligible fathers must have contact with at least one child, be able to understand and speak English, and have capacity to maintain participation and attend group work regularly, bearing in mind their substance use status. Mothers participating in trial and comparison programs are also eligible for the study.

The trial program (KODY) will constitute fathers referred for their problematic AOD use and identified by AOD case managers as using DV, or at risk of using DV. KODY fathers must be receiving support through Odyssey House Victoria clinicians. These men, their children with whom they have contact, and the children’s mothers, will be offered support through *Kids in Focus* as part of the intervention group. The comparison group will comprise fathers who are referred (or self-refer) to a ‘*Caring Dads* standard’ program. These fathers will have been identified as using DV or being at risk of using DV.

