### Secondary outcomes and measures

The secondary outcome of fathers’ use of DV relates directly to the primary outcomes of improved safety and wellbeing for women and children, as DV is seen as a major risk. Further, the secondary outcome of fathers’ use of AOD, will also contribute to the primary outcomes, given the evidence that where fathers use both DV and AOD, the severity of abuse, and therefore the risk to safety is significantly higher [1]. The secondary outcome of fathers’ use of DV will be assessed through reporting from fathers and mothers, using an adapted Mirabal measure, the Anger Management Scale, and the Brief Irritability Test.

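### Arm is tied to AOD status by the entry rules, so adjustment for baseline AOD use in the primary comparison should not be conditional

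*Protocol article*

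**What the plan says.** Under Eligibility criteria the article defines the population of interest: "The target group for study is fathers who use DV and AOD". The study-level entry rule is wider: "Fathers and their (ex)partners eligible to participate in either the trial or the comparison programs will be eligible for the study". The two arms then have different rules.

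- **KODY:** "fathers referred for their problematic AOD use and identified by AOD case managers as using DV, or at risk of using DV". In addition, "KODY fathers must be receiving support through Odyssey House Victoria clinicians".
- **Comparison (Caring Dads standard):** fathers are referred or refer themselves, and "These fathers will have been identified as using DV or being at risk of using DV". No AOD condition is set.

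The only substance-use wording that applies to both arms is that fathers must "have capacity to maintain participation and attend group work regularly, bearing in mind their substance use status". This qualifies their ability to attend; it does not require AOD use.

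The article treats AOD as prognostic. Background names it among the few consistent predictors of whether men continue or stop using violence. Secondary outcomes and measures says that "where fathers use both DV and AOD, the severity of abuse, and therefore the risk to safety is significantly higher".

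Data analysis acknowledges that fathers are not randomised. It plans to compare the groups at T1 and to use propensity analyses only if that comparison shows a need.

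**The concern.** The primary aim concerns mothers and children affected by men with problematic substance use. As the rules stand, every KODY family meets that description and a comparison family need not. The imbalance comes from the entry rules and not from chance, and it falls on a variable that the article links both to the severity of abuse and to whether it persists. Because AOD is linked to persistence, adjusting for the baseline abuse score alone may not be enough.

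A rule that triggers adjustment only when imbalance is found suits imbalance that might or might not arise. Here the imbalance on AOD is largely known before the first father enrols. An unadjusted between-group difference in women's or children's safety, or the lack of one, could partly reflect AOD-affected families being set against a mixed group. A larger sample recruited under the same rules would not remove that.

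**Working it through.** **1. The plan's own figures.** Recruitment and sampling gives a medium Cohen's d, power 0.80, a two-tailed test, 64 mothers per arm, a 75% partner contact rate and 170 families. Neither d nor alpha is printed; I assume d = 0.5 and two-sided alpha = 0.05. A two-sample t calculation gives 63.8, so 64 per arm and 128 in total (power 0.801). Enrolment is 128 / 0.75 = 170.7, against 170 stated, a rounding difference. The sample-size arithmetic is sound.

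**2. AOD prevalence by arm.** In KODY it is 100% by the entry rule. For the comparison arm the article gives no figure. The nearest is in Background, where the earlier Australian Caring Dads "evaluation for fathers who use violence found that a third of participants were accessing AOD services". That is service contact in another sample, so 1/3 serves only as a proxy and I vary it below.

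**3. Bias of an unadjusted comparison.** Let AOD use shift the outcome by g SD (assumed; not in the article) and let f be the comparison-arm prevalence. Then bias = g × (1 − f).

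| g (SD) | f = 0.2 | f = 1/3 | f = 0.5 |
|---|---|---|---|
| 0.2 | 0.16 | 0.13 | 0.10 |
| 0.3 | 0.24 | 0.20 | 0.15 |
| 0.5 | 0.40 | 0.33 | 0.25 |

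At f = 1/3 the bias is 0.13/0.5 = 27% to 0.33/0.5 = 67% of the planned effect.

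**4. Consequences at 64 per arm, f = 1/3.**

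- If the bias runs against KODY, a true d of 0.5 appears as 0.37, 0.30 or 0.17 for g = 0.2, 0.3 and 0.5. Power becomes 0.54, 0.39 or 0.16.
- If it favours KODY, the same true d appears as 0.63, 0.70 or 0.83.
- With no true effect, the probability of a significant result in either direction is 0.116, 0.202 or 0.465 instead of 0.05.

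**5. Comparison among AOD-using fathers only.** Keep all 64 KODY mothers and the share f of the 64 comparison mothers, with d = 0.5:

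| f | Comparison mothers | Power | Detectable d at 80% power |
|---|---|---|---|
| 1/3 | 21 | 0.50 | 0.71 |
| 1/2 | 32 | 0.63 | 0.61 |
| 3/4 | 48 | 0.74 | 0.54 |

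Reaching 64 such mothers at f = 1/3 would take 64 / (1/3) = 192 comparison mothers, or 192 / 0.75 = 256 families. Planned capacity is 3 groups × 10 fathers × 3 years = at most 90 comparison fathers.

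**The case against.** The strongest reply is that the plan already contains much of the remedy. Non-randomisation is stated and justified, a T1 comparison is promised and propensity analysis is foreseen. Table 1 lists AUDIT and DUDIT as fathers' measures, and Data collection schedules the measures at T1 with no restriction by arm. The choice of covariates and overlap diagnostics commonly belongs in a statistical analysis plan, which is not at hand. All of that stands. What remains is a condition that the article does state: adjustment depends on a later judgement of need, although its own entry rules make the imbalance foreseeable.

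A reader might also infer more than the article supports.

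- **That the arms do not overlap on AOD, so propensity methods must fail.** Recruitment and sampling lists Odyssey House programs and other AOD services among the referral sources for both programs, so some overlap is plausible.
- **That most comparison fathers lie outside the target group.** The one-third figure counts service contact in an earlier evaluation. It misses men who use AOD without treatment and does not describe this arm.
- **That the bias runs against KODY.** More severe families may do worse at follow-up, or may have more room to improve. The outcome is framed as improvement, T1 scores are collected, and the article does not settle the direction.
- **That Odyssey support is purely a nuisance factor.** The intervention section describes KODY as integrating both agencies' work, with AOD practitioners in case coordination, so this support is at least partly the intervention.
- **That the primary analysis must be restricted to AOD users.** This is a debatable trade-off. It could cut power to about 50%, and a common AUDIT/DUDIT threshold might also exclude KODY fathers whose use has fallen under support. The 64 v 21 figure assumes none are lost.

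**Conclusion.** The concern holds in a limited form. The target-group sentence and the comparison-arm entry rule do not agree, and together the entry rules associate arm with a factor that the article calls prognostic. Making adjustment conditional is therefore badly fixed. For f = 1/3 and g between 0.2 and 0.5 SD, the bias in an unadjusted comparison is about 0.13 to 0.33 SD, in a direction that the article does not determine. Both f and g are assumptions, as are d = 0.5 and alpha = 0.05, although the last two reproduce the stated 64 per arm.

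The confounding is built in but need not be total, and measured AOD severity can be adjusted for where the arms overlap. Adjustment cannot separate the effect of support from Odyssey clinicians, because that support is required in one arm only. It does not follow that the study is uninformative. Its contrast is KODY together with Odyssey AOD support against Caring Dads standard, and attribution should be limited to that.

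**What to change.** 1. Reconcile the target-group sentence with the comparison-arm entry rule under Eligibility criteria, so that the population of the primary comparison is stated once and the same way for both arms.
2. In Data analysis, make covariate adjustment or overlap/propensity weighting unconditional in the primary comparison. Always include T1 AUDIT, T1 DUDIT and the T1 score of the outcome analysed.
3. Report overlap on these variables and the effective sample size after weighting.
4. Give the comparison among fathers with baseline AOD use in both arms as a sensitivity analysis. State its lower power: about 50%, 63% or 74% for d = 0.5 if the comparison-arm share is 1/3, 1/2 or 3/4.
5. Describe the contrast as including Odyssey AOD support and word the conclusions to match.

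The cost is small: the measures are already scheduled at T1, so these are changes of wording and analysis. The downside is some loss of effective sample size and a less favourable statement of precision than 64 per arm suggests.
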